#### Intervention conditions

##### Condition 1: Blended MI and PST for alcohol

The overall goals of this blended intervention are to motivate participants to reduce their hazardous or harmful drinking and equip them with problem-solving skills that will improve their ability to cope with alcohol use triggers. This experimental condition will comprise four modules conducted over two sessions, with these sessions spread one week apart (Table 1). These four sessions allow us to cover all of the core principles of PST and allow time for practicing of skills. In formative research to determine the appropriateness and acceptability of our MI-PST intervention for patients attending primary health care services, one hour was the most preferred session length, and the vast majority of patients were willing to return to the clinic for two to three extra visits. Hence we have tailored this intervention to meet patients’ preferences [45]. Each session iteratively builds upon participants’ readiness to change and the problem-solving and coping skills developed in the previous session, and has a motivational, educational and practical component. The sessions’ structure conforms to our previous research observations that ART recipients most preferred one-hour long sessions, and two-session interventions.

**Table 1 Tab1:** **Blended motivational interviewing (MI) and problem solving therapy (PST) intervention**

	Summary of blended MI and PST sessions and objectives
**Session 1, Week 1** 45 minutes	• Conduct screening/assessment of alcohol use
	• Provide feedback on results of screening/assessment
	• Increase knowledge of how alcohol use impacts on course of HIV
	• Use MI to build rapport and develop readiness to change
	○ Assess readiness to change (using readiness ruler)
	○ Assess pros and cons of change (Decision-balance exercise)
	○ Use MI to try and shift participant and elicit a commitment to change
**Session 2, Week 1**	Patient check-in (using MI)
50 minutes	• Build the Rationale for PST
	• Explain the structure of PST
	• Explain the link between problems and alcohol use, and the rationale for PST
	• Establish positive problem orientation
	• Describe the steps of PST
	• Build the rationale for activity scheduling
	• Describe the steps of Problem Solving
	• First Problem Solving Session with counsellor (using the steps) and describe homework
**Session 3, Week 2** 50 minutes	• Patient check-in (using MI)
	• Review homework from previous week and challenges/difficulties
	○ Elicit positive change talk and affirm commitment to change using MI techniques
	○ Review PST steps and affirm attempts to change
	• Explain what can be done about problems that are not important (coping with negative thoughts)
	• Second Problem Solving Session with counsellor and an exercise
**Session 4 Week 2** 45 minutes	• Review practice exercises from session 3
	• Explain what can be done about problems that are important but cannot be solved 5 min (advancing the process of acceptance)
	• Third Problem Solving Session with counsellor and recap
	• Elicit positive change talk and affirm commitment to change using MI techniques

##### Condition 2: Blended MI-PST for wellness

The wellness intervention will be an equal attention-control arm. Like the alcohol reduction intervention, this intervention will incorporate MI-PST techniques to promote reduction of health risk behaviours, healthy nutrition and a healthy lifestyle. It will be delivered across four sessions, with Sessions 1 and 2 occurring in Week 1 (separated by a break) and Sessions 3 and 4 occurring in Week 2. Participants will be taught about healthy eating, to maintain a healthy weight, and the value of exercise for optimum health.

##### Condition 3: Treatment as usual (TAU)

Participants in this condition will receive the standard package of care for PLWHA and on ART who also drink at hazardous/harmful levels. Typically, if a health care provider suspects adherence problems (by self-report or clinical indicators), the patient is referred to adherence counsellors for additional counselling. There are no firm guidelines on the duration or content of this counselling. Counsellors are left to determine how best to address adherence problems with the patient. If adherence counsellors or primary health care providers suspect alcohol problems, they usually refer patients to on-site clinical psychologists/clinical social workers, if available, or off-site community mental health (CMH) or alcohol services. We will monitor the number of visits the TAU patients make for adherence and alcohol support, and type(s) of support services received (e.g. advice, referral) by means of self-report at the 3, 6, and 12 month follow-ups.

#### Follow-Up

Participants will be followed-up on three occasions: at three, six and 12 months (Table 2). At each follow-up visit, they will be interviewed using a structured questionnaire. They will have blood drawn for the following tests: viral load (at baseline and 12-month follow-up); CD4-T cell count (at each follow-up point); and alcohol biomarker PEth (at each follow-up point). Compensation will be provided to participants in all arms in the form of shopping vouchers for completion of the follow-up assessments.

**Table 2 Tab2:** **List of study instruments, data elements and source of information**

Data collection instruments	Time period	Data collected	Source
Screening questionnaire	Day of enrolment	Eligibility assessment	Self-report
Participant assessment	Baseline 3, 6, and 12 month follow up	Demographic information, alcohol consumption, social problem solving styles, motivation/readiness to change, antiretroviral therapy (ART) history, adherence to ART, psychosocial factors associated with ART adherence (disclosure, HIV/AIDS stigma, social support, adherence self-efficacy), alcohol and ART beliefs, HIV-related factors (e.g. degree of ill-health between HIV diagnosis and ART initiation), clinical/structural factors (e.g. length of time to doctor), physical functioning (e.g. limitations due to physical health, bodily pain, vitality), general physical well-being, mental well-being, drug and tobacco use	Self-report
Laboratory report form	Baseline, 3, 6, 12 month follow up	HIV-related outcomes: viral load (baseline and 12-month follow up assessments only) and CD4 counts	Laboratory report
		Alcohol biomarkers: Posphatidylethanol (PEth)	
Process evaluation interview schedule	12-months follow-up	A randomly selected 10% subsample will respond to a qualitative interview regarding impressions of the degree to which the intervention helped or hindered behaviour change	Self-report

#### Participant retention

In order to enhance participant retention we will: (1) inform interested individuals at recruitment that participation in the study will last for 12 months, and that if they anticipate relocating to another area or clinic they will not be eligible to participate. (2) Ask participants to provide their own and two close relatives’ or friends’ contact details, including telephone numbers and physical addresses to facilitate regular contact with them, reminder calls, and other participant tracking efforts.

#### Measures

We will use a structured questionnaire at baseline and each follow-up period. It will be available in English, Afrikaans and seTswana. We will assess the following:

*Demographic Characteristics.* We will assess participants’ age, gender, race/ethnicity, income, education, employment status, housing status, relationship status, sources of income and food insecurity.*Alcohol Consumption.* Multiple self-report measures will be used to assess various dimensions of alcohol consumption. The Alcohol Use Disorders Identification Test (AUDIT) [46] will be employed as part of the initial screening process, as well as all further follow-up assessments to identify potential harmful and hazardous drinking. We will change the reporting period of the AUDIT from 12 months to 3 months at baseline and at each of the follow-up periods. We will only ask participants to respond to the AUDIT questions for the past 12 months during the screening. Additional items will assess current drinking/abstention (past 90 days, past 12 months and lifetime). The 3-month quantity item will serve as the primary behavioural outcome measures for alcohol consumption, together with a combined quantity-frequency measure.*Social Problem Solving Styles.* We will employ the 25-item Social Problem-Solving Inventory Revised-Short Form (SPSI-R: SF) [47], which measures problem solving styles. Previous South African studies have obtained Cronbach’s alphas of 0.72-0.83 for this scale [48].*Motivation/Readiness to Change.* The participants will be asked to respond to the 12-item Readiness to Change Questionnaire to determine their readiness to change their drinking behaviour [49].*Adherence to ART.* Four adherence measures will form the basis of the self-reported ART adherence outcomes: (1) The AIDS Clinical Trials Group (ACTG) adherence questionnaire; which assesses patients’ current ART medications, dosing schedule, and medication doses missed over the past four days [50]; (2) The Visual Analog Scale (VAS), which assesses general levels of adherence over a 30-day timeframe [51]. For the ACTG and VAS, adherence levels will be examined in terms of both continuous and dichotomous measures (e.g. cut-offs of 90%, 95%, and 100% adherence rates); (3) The CASE Adherence Index [52]; and (4) The Self-Rating Scale Item (SRSI) [53, 54].*Health Functioning.* The SF-8 is an eight item measure of health and well-being, assessing physical functioning, limitations due to physical health, bodily pain, general health, vitality, social functioning, limitations due to emotional health, and mental health issues [55].*Mental Well-Being.* The Kessler Psychological Distress Scale-10 [56] will be used to assess psychological distress.*Drug and Tobacco use.* The Drug Use Disorders Identification Test (DUDIT) [57] is an 11-item self-report measure that will be used to assess concurrent substance use. Participants will also be assessed for tobacco use (including lifetime, current and regular cigarette smoking) and tobacco dependence using the Fagerstrom Test for Nicotine Dependence (FTND) [58].*Alcohol Biomarkers.* In addition to the use of self-report measures of alcohol use, tests of the alcohol biomarker, Phosphatidylethanol (PEth) [59, 60] will be conducted among all participants at each time point.*Clinical/Structural Factors*. The following structural factors typically associated with ART adherence will be assessed: Time to doctor; difficulty getting to the clinic. These are reasons for difficulty getting to the clinic. Based on previous research with HIV clinic patients in South Africa [61].*HIV-Related Factors*. The following information will be obtained: perceived year and month of diagnosis; perceived current HIV viral load and CD4 cell count, advent of opportunistic infections, the degree of ill health between diagnosis and starting on ART, and the duration from diagnosis to ART enrolment.*ART History*. We will assess the duration of being on ART and duration on the current regimen.*Psychosocial Factors*. Psychosocial factors typically associated with ART adherence will be assessed. For example, HIV stigma will be measured with the Internalised AIDS-Related Stigma Scale [12], HIV disclosure will be assessed via a measure used in our prior studies [42, 44], social support will be assessed by the MOS Social Support Survey [62], and adherence self-efficacy will be assessed by the HIV Treatment Adherence Self-Efficacy Scale (HIV-ASES) [63].*General Physical Well-being*. The Karnofsky Performance Scale will be used to evaluate the general health/functional status of prospective participants. Scores range from 0 to 100; the lower the score, the more compromised general well-being [64, 65]. Individuals with a Karnofsky clinical score below 50 will not be eligible for participation.*Alcohol and ART*. We will ask about (1) the source(s) of participants’ knowledge about alcohol use and ART; (2) beliefs about alcohol and ART; (3) beliefs about the acceptability of drinking while on ART; and (4) patterns of drinking while on ART.*Screening for Cognitive Impairment*. We will use the International HIV Dementia Scale (IHDS) [66] to screen for substantial cognitive impairment. The cut-off score on this instrument is 10.

### Phase 3: process evaluation

Following the final follow-up assessment, we will randomly select 10% of participants (from the wellness and MI-PST conditions) for qualitative in-depth interviews. These interviews will assess participants’ impressions of the degree to which they felt the intervention helped or hindered behaviour change. They will be conducted by project staff not involved in the assessments or interventions in order to minimise response bias. The qualitative interviews will be conducted in the participants’ language of choice. All interviews will be audio-taped and transcribed verbatim. Findings from these qualitative interviews will be used to interpret and better understand the quantitative findings from the RCT. Participants will receive an incentive for their time and participation in these interviews and a voucher to cover transport costs.

### Study timeline

The first nine months of the study will involve intervention and measurement development, piloting of intervention components and training field staff and counsellors. Study recruitment will be conducted at the end of Year 1 and during the first 3 months of Year 2. If necessary, timelines may be adjusted based on information gained during the pilot phase. Intervention sessions will commence in the last quarter of Year 1 and continue during the first half of Year 2. Three and six month follow-up assessments will be conducted in Year 2. Twelve-month follow-up assessments will be conducted in Year 3. Quarters 3–4 of Year 3 will involve data synthesis, analysis, write-up and dissemination.

### Statistical treatment and analysis of data

#### Analyses for phase 1

All audiotapes will be transcribed into MS Word. MS Word documents will be imported into Nvivo 10 [67]. Data analysis will be conducted using the framework approach (familiarization, identifying a thematic framework, indexing, charting, mapping and interpretation). Initially, transcripts will be read for emergent themes, which will then be coded. Coding and analysis will continue iteratively as new themes and issues emerge; all relevant information will be retrieved and examined for further coding designations. To establish inter-coder reliability, each transcript will be coded by at least two individuals. Coding discrepancies will be discussed and resolved and transcripts will be subjected to checks until the Cohen’s Kappa score reaches 70% agreement. We will use these findings to assist with revisions to our proposed intervention materials and implementation protocols.

#### Analyses for phase 2

Given the repeated measures design, the main statistical analysis will involve repeated analysis of variance and analysis of covariance, using pre-treatment means and post-treatment means; or two-sample t-tests or chi-squared tests at the patient level data. The hypothesis that alcohol reduction will increase adherence will be tested via a repeated-measures Analysis of Variance (ANOVA). This will be an intent-to-treat (ITT) analysis. For our ITT analysis we will analyse our data based on the participants’ original allocation to the groups regardless of any subsequent group changes or participants’ degree of adherence to study protocols or their withdrawal from the study. We will assume data will be missing completely at random (MCAR) in order to enable imputation of missing data using standard techniques. We have postulated a main effect for the experimental condition without an interaction effect. In addition, we intend to use the CD4 T-cell counts and viral loads as objective biological endpoints, with the same statistical procedure being employed. Additional analyses will determine whether the pathway via reduction of alcohol consumption was indeed crucial to the differences in adherence. This can be measured by a cross-lagged panel design, where the alcohol in the time interval before the respective measurement of adherence will be assumed to have a significant effect. Structural equation modelling and path analysis will be used to test this assumption. Models will also be run with ART continuation as the endpoint. More advanced techniques, including generalised estimating equation and multilevel modelling, will also be employed. The association between the biomarker of alcohol consumption and self-reports of alcohol will be analysed using correlation and regression techniques with adjustments for possible confounders. The predictive ability of the biomarker will be assessed using sensitivity and specificity techniques to determine its ability to detect excessive self-reported consumption of alcohol.

#### Analyses for phase 3

Data analysis will be conducted using the same framework approach as described above for Phase 1. We will use the Phase 3 findings to assist with interpreting the findings of the RCT phase.

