Sample size estimates are based on the numbers of patients needed to detect differences between intervention and control groups in the mean number of drinks per day (past 30/60 days) at 3, 6, and 12 months post randomisation, our main outcome measure. A study among HIV patients found that the mean number of drinks per drinking days was 3.58 (Standard Deviation (SD): 1.81) under an enhanced MI vs. 4.75 (SD: 3.22) under the control arm [43]. For two-sided testing at a significance level of 5% and power of 90%, with one pre- and three post- intervention measures with a within subject correlation of 0.7 between measurements, the required sample size using analysis of covariance methods is 260. Of the 260 participants, 130 will be allocated to the alcohol intervention and 65 to each of the wellness and TAU arms. This imbalance of sample sizes for the treatment combinations can cause loss of power of statistical tests of differences between the group outcomes (e.g. means). It may also produce sensitive results in small samples when the assumptions of equal variance between groups are violated. Nonetheless, our choice of the imbalanced design was based on valid scientific and practical reasons, as the intervention combination we plan to assess is of great interest. Thus, the higher sample size in the main intervention arm (alcohol intervention) was chosen as it is statistically more efficient to have more subjects in this group as we will be comparing its effect to each of the other two interventions. This sample size also allows adequate power (>90%) to detect a modest effect size (0.25) for the within-subjects component, and for a potential interaction between- and within-subjects factors. However, the actual number of participants needs to be inflated to take into account attrition over time. We estimate an overall attrition rate of 20% and therefore need to recruit 325 participants to take into account this attrition. Assuming four sites, this would create a site-specific sample size of 82 (66 after attrition).

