We have no site-specific hypotheses, but if we want to include a safety margin for testing site specific effects of 0.30, we should allow for a site specific sample of 150 which would already include the attrition (120 per site before attrition). Of these, 75 would receive the alcohol intervention, and 38 each the wellness intervention and TAU. We will recruit participants from each site without an attempt to have equal numbers of men and women; we anticipate a ratio of about 2:1 females to males. Based on our prior data [44], we would estimate that about 40% of ART recipients will be alcohol drinkers. Of the alcohol drinkers, we estimate that about 15% would meet the criterion related to alcohol (have six (or four, if female) or more drinks on one occasion at least weekly, and score no more than 22 on the AUDIT). That research also suggests a participant eligibility rate of no more than 20%, so we would need to screen at least 750 patients at each site to reach our target sample of 150. Therefore we need to recruit participants from large facilities, suggesting that only hospital-based clinics would qualify as possible study sites. Thus, we plan to recruit participants from all four of the district hospitals in the Tshwane Health District, which cover a wide catchment area. The hospitals are: (1) Tshwane District Hospital, (2) Pretoria West Hospital, (3) Odi District Hospital, and (4) Jubilee Hospital. With four sites, our final sample size of 600 will include 300, 150 and 150 participants in the alcohol, wellness and TAU arms respectively. In the proposed district hospitals, there are HIV clinics in the form of separate outpatient departments (OPD). These HIV clinics carry very high volumes of patients, spanning the whole continuum of care.

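### The plan assumes data are missing completely at random so that it can impute; imputation does not need that assumption, and it is hard to defend in this trial

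*Protocol article*

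**What the plan says.** Under Analyses for phase 2, the protocol article commits to an intention-to-treat analysis that keeps withdrawn participants in their allocated group. It then gives the missing-data basis: "We will assume data will be missing completely at random (MCAR) in order to enable imputation of missing data using standard techniques". No imputation method is named.

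On the model, the same paragraph says that "the main statistical analysis will involve repeated analysis of variance and analysis of covariance", and it offers two-sample t-tests or chi-squared tests as alternatives. Generalised estimating equations (GEE) and multilevel models appear later in the paragraph as further techniques.

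The section Study population and sample size considerations expects 20% attrition ("We estimate an overall attrition rate of 20" per cent). It concludes that the trial would "need to recruit 325 participants to take into account this attrition" and then settles on a larger trial: "our final sample size of 600 will include 300, 150 and 150 participants in the alcohol, wellness and TAU arms respectively".

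**The concern.** The sentence gives a reason for the assumption, and the reason is mistaken. Multiple imputation and likelihood mixed models on all available visits are valid under MAR, where loss may depend on anything observed, including arm and earlier drinking. If MCAR did hold, imputation would not be needed to avoid bias.

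MCAR says that loss is unrelated to drinking, adherence, health or arm. The article itself points the other way:
- The Background reports that problem drinkers were only 47% as likely to be adherent to ART as non-problem drinkers or abstainers, so drinking goes with disengagement from treatment.
- Recruitment procedures asks the alcohol and wellness arms, but not treatment as usual, to come back for intervention sessions. The visit burden therefore differs by arm.

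The primary outcome is drinking. If loss depends on drinking differently by arm, a method that relies on MCAR gives a distorted treatment effect. The earlier drinking measurements that could correct this are already scheduled.

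**Working it through.** **The plan's own figures.** Attrition inflation: 260 / (1 − 0.20) = 325, as stated. For the final size, 600 × 0.80 = 480, so about 120 participants could lack complete follow-up.

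**Check 1, in SD units.** The correlation of 0.7 comes from the sample size section ("with one pre- and three post- intervention measures with a within subject correlation of 0.7 between measurements") and the 20% loss from the attrition estimate. The true effect of −0.30 SD and the dropout mechanisms are my assumptions, because the article gives none. Drinking at baseline, month 3 and month 12 is normal with SD 1 and all correlations 0.7. The effect is present at months 3 and 12. Loss at month 12 follows logit P(missing) = c + b × (month-3 drinking, standardised within arm), with c set in each arm to give 20% loss. There are 2 million participants per arm, so sampling error is negligible.

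| Slope b (alcohol arm, comparator) | Completers, baseline-adjusted | Error |
|---|---|---|
| 1, 1 | −0.30 | about 0 |
| 0.5, 0.5 | −0.30 | about 0 |
| 0.5, 0 | −0.319 | 0.319 / 0.30 = 1.06, 6% too large |
| 1, 0 | −0.337 | 0.337 / 0.30 = 1.12, 12% too large |
| 1, −1 | −0.375 | 0.375 / 0.30 = 1.25, 25% too large |

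In the (1, 0) case the unadjusted completers' t-test gives −0.42 (0.42 / 0.30 = 1.40, 40% too large). Imputing by arm from baseline and month 3 gives −0.30 in every row.

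A hand check agrees. In the (1, 0) case, selection shifts the completers' month-12 mean in the alcohol arm by 0.42 − 0.30 = 0.12. Their baseline mean shifts by the same amount, because both correlate 0.7 with month 3. Adjustment with a slope of about 0.7 removes 0.7 × 0.12 and leaves 0.12 × (1 − 0.7) = 0.036, giving 0.336. With opposite directions the residue doubles: 0.30 + 0.072 = 0.372, close to 0.375.

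**Check 2, on the planning scale.** The cited study found that "the mean number of drinks per drinking days was 3.58 (Standard Deviation (SD): 1.81) under an enhanced MI vs. 4.75 (SD: 3.22". The difference is 4.75 − 3.58 = 1.17, and the SD is √[(1.81² + 3.22²) / 2] = 2.61. I simulated 300 v 150 participants with four measures, correlation 0.7, true difference −1.17, about 20% missing at 12 months and 1,500 replicates per mechanism.

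| Mechanism (assumed) | Completers' t-test | Completers' ANCOVA | Imputation from arm and earlier drinking |
|---|---|---|---|
| MCAR | −1.18 | −1.18 | −1.18 |
| Loss rises with 6-month drinking, same rule in both arms | −1.08 (8% too small) | −1.14 (3% too small) | −1.17 |
| Same, alcohol arm only (21% v 19% missing) | −1.51 (29% too large) | −1.28 (about 10% too large) | −1.18 |
| Loss depends on the unseen 12-month value, alcohol arm only | −1.62 | −1.41 | −1.35 |

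In the second row the same rule loses 18% of the alcohol arm and 24% of the comparator, because the intervention lowers drinking. Filling gaps with the arm mean reproduces the −1.51 of the third row, and its nominal 95% interval covers the true value only 52% of the time.

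**The case against.** The strongest reply is that an assumption does not bias anything; the method applied does. The plan commits to imputing, and multiple imputation is a standard technique. If earlier drinking were in the imputation model, the result would be protected under MAR whatever label the protocol used. The choice of method may properly sit in the full protocol or the statistical analysis plan. All of this stands.

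A reader might infer stronger things that the article does not support:
- *That the primary estimate will be biased.* This needs loss that depends on drinking, a method valid only under MCAR and, for the larger errors, different dropout behaviour by arm. When the rule is the same in both arms, the adjusted completers' error is between nil and about 3%.
- *That repeated-measures ANOVA will discard anyone with a missed visit.* The same paragraph says that missing values will be imputed.
- *That mean or other single imputation is planned.* Pooled-mean imputation would shrink the effect by 20% even under MCAR (0.80 × 0.30 = 0.24), but it is not named.
- *That a 25% error is likely.* It requires heavier drinkers to leave one arm and lighter drinkers the other, and nothing in the article suggests this.

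The multilevel model is a partial safeguard, since a likelihood fit on all visits is valid under MAR. It is listed as an additional technique, however, and unweighted GEE generally does need MCAR. The objection does not rescue the sentence: it is a stated position with a wrong reason, not a detail deferred to another document.

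**Conclusion.** The point holds as a wrongly justified and implausible assumption that leaves the primary analysis less protected than it need be. It should be fixed, but it is not a fatal flaw. The wording error is certain. The size of any harm is not, because it depends on an unnamed method and an unknown dropout mechanism. The range runs from small or no error under a common mechanism, through 6% to 12% (adjusted) or up to 40% (unadjusted t-test) when loss depends on drinking in the alcohol arm only, to 25% (adjusted) in the extreme opposite-direction case.

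Two limits apply. The calculations assume that an interim drinking measurement exists for those later lost; participants lost before month 3 have only baseline to draw on. MAR is also not a complete safeguard: when loss depended on the unseen value, MAR imputation was still about 15% too large (1.35 / 1.17 = 1.15).

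**What to change.** Delete the MCAR sentence and put in its place, for example: *The primary intention-to-treat analysis assumes that data are missing at random given arm, site, baseline and observed follow-up data. It uses a likelihood mixed model on all available visits, or multiple imputation carried out by arm with baseline and interim drinking, PEth and site in the imputation model.* One of the two should be chosen before data are seen. The mixed-model option promotes the multilevel model already planned from an additional to the main analysis.

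A sensitivity analysis for data missing not at random, such as one assuming heavier drinking among those lost, is desirable but secondary. Its absence from the article is not a fault.

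The cost is a change of wording and some programming. Drinking and PEth are already scheduled at baseline and at 3, 6 and 12 months, so sample size, visits and data collection do not change.

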#### Randomisation and blinding

Randomisation to one of the three conditions will occur at each of the four sites, i.e. the randomisation will be stratified by site. The randomisation code will be generated by computer generated tables. Treatment allocation will be done by site supervisors using pre-prepared consecutively numbered sealed, opaque envelopes, which will contain the group assignment. Fieldworkers will conduct the post-intervention outcome assessments masked to treatment allocation to ensure that the assessments remain unbiased and independent from the intervention sessions. Each counsellor will take part in only one intervention arm, and the wellness and alcohol reduction interventions will be run on different days of the week (based on alternating biweekly schedule) to minimise contact between participants who are randomly allocated to different arms, and to minimise contamination across the study arms. Given the study’s behavioural nature, the interventionists will not be blinded to which intervention the participants receive.

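### The trial is sized for ANCOVA, but the analysis section does not fix ANCOVA as primary and leaves open options that need about 1.3 to 4.4 times the patients

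*Protocol article*

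**What the plan says.** **Sizing** (Protocol article, Study population and sample size considerations). The calculation is for a two-sided 5% test with 90% power, "with one pre- and three post- intervention measures with a within subject correlation of 0.7 between measurements", using analysis of covariance. The assumed drinking levels are "3.58 (Standard Deviation (SD): 1.81) under an enhanced MI vs. 4.75 (SD: 3.22) under the control arm". The stated result is 260, split 130/65/65, or 325 after allowing for 20% attrition. A margin for site-specific effects then raises the planned total to 600 (300/150/150). The same section claims adequate power "for a potential interaction between- and within-subjects factors".

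**Analysis** (Statistical treatment and analysis of data, Analyses for phase 2). The main analysis "will involve repeated analysis of variance and analysis of covariance, using pre-treatment means and post-treatment means; or two-sample t-tests or chi-squared tests" on patient-level data. Repeated-measures ANOVA alone is named for the adherence hypothesis. The section then says: "We have postulated a main effect for the experimental condition without an interaction effect". Generalised estimating equations and multilevel models are mentioned as further techniques.

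**Design features** (Randomisation and blinding). The article says that "the randomisation will be stratified by site" and that "Each counsellor will take part in only one intervention arm".

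**The concern.** The analysis section joins its options with 'or', and those options differ widely in efficiency. ANCOVA uses the 0.7 correlation with baseline, a t-test on follow-up values throws it away, and a chi-squared test needs the continuous drinking outcome to be cut into categories.

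The no-interaction sentence adds a second ambiguity. The design has one observation before and three after the intervention. If all four are levels of the repeated factor, randomisation makes the arms equal in expectation at the first. A treatment effect then shows as arm by time, and the arm main effect is diluted by a quarter.

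Two things are at stake. The power stated for ANCOVA does not carry over to the other options. And a choice of test left open until the data are seen weakens control of the type I error.

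**Working it through.** **Inputs from the sample size section:** difference 4.75 − 3.58 = 1.17; SDs 1.81 and 3.22; correlation r = 0.7; one pre and three post measures; two-sided 5%; 90% power; 2:1 allocation in each pairwise comparison. **Assumptions:** compound symmetry, no baseline difference, constant effect over follow-up, normal approximation, no multiplicity adjustment, and the cited difference and SDs taken as given for one visit.

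**1. The plan's own figure.** The ANCOVA variance factor is (1 + 2r)/3 − r² = 0.80 − 0.49 = 0.31. The control-arm size is (1.960 + 1.2816)² × (1.81²/2 + 3.22²) × 0.31 / 1.17² = 10.507 × 12.006 × 0.31 / 1.3689 = 28.6. Over a 2:1:1 design that is 4 × 28.6, about 115. With SD 3.22 in both arms it is about 148. The stated inputs therefore do not reproduce 260; the attrition step does (260/0.8 = 325). This is a separate point. It matters here only because ANCOVA at 260 cannot be taken to sit at exactly 90% power.

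**2. Variance factors (relative to the single-visit variance).**
- t-test on change in means: 0.80 + 1 − 2 × 0.7 = 0.40
- t-test on the mean of three follow-ups: (1 + 2r)/3 = 0.80
- t-test at a single visit: 1.00
- arm main effect over four visits: variance (1 + 3r)/4 = 0.775 on 0.75 of the effect, equivalent to 0.775/0.75² = 1.378

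**3. Patients needed relative to ANCOVA.** Divide each factor by 0.31. These ratios depend only on r and the number of visits, not on the effect size or on whether 260 is right.

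**4. Power.** Power is Φ(1.17/(SE × √factor) − 1.96). At 130 v 65 with the stated SDs, SE = √(1.81²/130 + 3.22²/65) = 0.430, so 1.17/SE = 2.72. For the four-visit main effect, 0.75 × 2.72/√0.775 = 2.32, and Φ(2.32 − 1.96) = 64%. The pair 240 v 120 is 300 v 150 after 20% attrition. Figures in brackets use SD 3.22 in both arms.

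| Analysis | Patients v ANCOVA | Power, 130 v 65 | Power, 240 v 120 |
|---|---|---|---|
| ANCOVA | 1 | 99.8% (99.0%) | >99.9% (>99.9%) |
| t-test, change in means | 1.3 | 99.0% (96.6%) | >99.9% (99.9%) |
| t-test, follow-up mean | 2.6 | 86.1% (76.2%) | 98.5% (95.3%) |
| t-test, single visit | 3.2 | 77.7% (66.7%) | 95.9% (90.1%) |
| Four-visit arm main effect | 4.4 | 64.0% (53.1%) | 88.3% (79.1%) |

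**The case against.** Much of the opposing case stands.

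- **ANCOVA is named.** A reader might infer that the main analysis excludes the method used for sizing. It does not: ANCOVA on pre- and post-treatment means is listed first, with repeated analysis of variance. The defect is that it is one option among several.
- **The no-interaction sentence has a sound reading.** It can mean a constant arm effect over the follow-up visits, which fits ANCOVA on means. Nor does allowing power for a potential interaction contradict postulating none. But the article does not say which visits the sentence covers.
- **The simpler tests may be meant for other outcomes,** such as categorical ones. The text does not limit them in that way.
- **The planned total is 600.** At that size both follow-up t-tests reach 90% or more on the protocol's own figures. Only the four-visit main effect stays below.
- **A collapse in power is not supported.** A reader might assume that ANCOVA has exactly 90% power at 130 v 65 and infer about 34% for the four-visit main effect and 44% for a single-visit t-test. That requires a standardised effect of 0.274, which the article does not state. Its own inputs give ANCOVA 99% or more at that size, and the inference ignores the 600.
- **Site and counsellors.** A condensed article may leave model terms to a fuller document, and multilevel modelling is mentioned. A reader might infer a large type I error from counsellor clustering, but the article gives no intraclass correlation and no caseload, so no size can be put on it.

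**Conclusion.** The point holds in a limited form. The article does not fix one primary analysis that matches its ANCOVA sizing, and its no-interaction sentence is ambiguous for any model that includes baseline as a repeated measure. The efficiency ratios of 1.3 to 4.4 are the firm result, given r = 0.7 and compound symmetry. The power figures also rest on the cited difference and SDs. On those, ANCOVA is amply powered at either size. The weaker options fall to 53–86% at 130 v 65, and at 240 v 120 only the four-visit main effect misses 90%.

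This should be corrected, but it does not undermine the trial: ANCOVA is already among the listed methods and the planned sample is large.

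**What to change.** In Analyses for phase 2, name one primary analysis for the drinking outcome: an ANCOVA or mixed model of the 3-, 6- and 12-month values, adjusted for the baseline value and for site as the randomisation stratum. Make the average arm difference over the three follow-ups the primary contrast. Delete the t-test and chi-squared alternatives for that outcome. State that the main effect without interaction refers to the post-randomisation visits only, and align this with the interaction remark in the sample size section.

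Because counsellors are nested in arm, add a sensitivity analysis with a counsellor random effect in the two counselled arms.

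The cost is wording only. Baseline values, follow-up values and site are available by design; counsellor identity needs to be on file for the sensitivity analysis, where intervals may be slightly wider.
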